**Methods:**

This is a monocentric prospective observational survey-based study. We will conduct an exploratory online/telephone survey about PAD in somatic vs. mental illness in Switzerland. The survey sample will comprise 10,000 Swiss residents of the general population from all three language regions (German, Italian, and French) as well as 10,000 medical professionals working in the seven states (“cantons”) of Basel-Stadt, Basel-Landschaft, Aargau, Lucerne, Graubünden, Ticino, and Vaud. Opinions on PAD in mentally and somatically ill patients will be assessed using 48 different case vignettes. Each participant will be randomly assigned a somatic terminal, a somatic non-terminal, and a mental non-terminal case vignette. Furthermore, the attitude toward the ethical guidelines of the Swiss Medical Association of 2004, 2018, and 2022, as well as the stigmatization of mentally ill people will be assessed.

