### Sample characteristics

For this study, we will survey a group of 10,000 Swiss residents from the general population including the three language regions (German, Italian, and French) as well as a group of 10,000 physicians practicing in the states (“cantons”) of Basel-Stadt, Basel-Landschaft, Aargau, Lucerne, Graubünden, Ticino, and Vaud. In total, the sample thus comprises 20,000 individuals. For each of the two groups, we performed a case number estimation to determine the size of a significant sample. For the group from the general population, our case number estimation showed that a sample size of *n* = 2,373 yields significant results at a 95% confidence interval and a margin of error of 2%. Based on the literature and our empirical values, we assume a response rate of 30%, which corresponds to 3,000 valid records for 10,000 persons and thus harmonizes with our estimated representative sample size. We also performed a case number estimation for the group of medical professionals, which indicated a sample size of *n* = 2,258 as significant at a 95% confidence interval and a margin of error of 2%. According to the 2019 FMH statistics, we plan to survey 10,000 physicians. Therefore, with a response rate of 30%, we can expect 3,000 valid data sets.

Eight thousand residents from the state of Basel-Stadt are to be randomly drawn from the state's register and contacted via postal mail. Furthermore, a sample of 2,000 individuals of the general population from the Italian- and French-speaking parts of Switzerland will be recruited by a polling institute. For the survey of the 10,000 physicians from Basel-Stadt, Basel-Landschaft, Aargau, Lucerne, Graubünden, Ticino, and Vaud we rely on the cooperation with the responsible health departments.

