### Data collection methods

The online survey will be created and administered using the online survey tool “Unipark” (Tivian XI GmbH, released 2020, Unipark, Köln, Germany: Tivian XI GmbH). The survey data will then be exported to Excel for storage.

The telephone survey in the Italian- and French-speaking parts of Switzerland will be conducted by a polling institute. Telephone survey data will be entered into the Unipark online survey as well and extracted to Excel for storage.

Project data will be handled with the uttermost discretion and is only accessible to authorized personnel who require the data to fulfil their duties within the scope of the research project. On the Case Report Forms (CRFs) and other project-specific documents, participants are only identified by a unique participant number. Data will be stored and used according to the Swiss Data Protection Act. The survey is anonymous, and no identifiable information will be stored. The data will be stored in an encrypted and password-protected Excel file which only the research team will have access to. They are subject to the duty of confidentiality. The data is stored in the internal clinical data system which aligns with the security standards for patient data in Switzerland.

In addition, we will regularly save a copy of this file on a CD to be able to track changes in the data at a later point in time. We keep dated and signed CDs in a safe. Only the research team can open this safe. To allow follow-up studies, the anonymized data will be kept indefinitely.

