### Survey administration

Participants from the general population will be recruited via postal mail as well as via a polling institute. Medical professionals will be recruited and contacted via email.

Those participants from the general population who will be contacted by postal mail will receive a QR code that will take them to the online survey. Participants from the medical profession will be directed to the online survey via a link that they will receive by email. The QR code or link will be used to access the survey start page, where the study will be described in detail and individuals are informed regarding participation. To start study participation, individuals must click the consent button. Only then will the survey begin. Individuals who do not wish to participate may, but are not required to, provide a reason. Persons from the general population contacted by telephone will be verbally informed about the study and asked for their consent before the survey begins.

Participants can complete the online questionnaire within 3 months. Once the survey period will be completed, the data will be analyzed within approximately 3 months, discussed, and summarized in a publication within another 3 months. In total, the research project is planned to take 14 months.

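### The Swiss general-population sample is Basel-Stadt online plus the French- and Italian-speaking regions by telephone: pooled levels are not national, and the public-versus-physician comparison mixes group with canton and mode

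*Protocol article*

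**What the plan says.** In the Abstract (Methods), the public sample is "10,000 Swiss residents of the general population from all three language regions". Sample characteristics repeats this: "we will survey a group of 10,000 Swiss residents from the general population including the three language regions (German, Italian, and French"). The Objectives and the Primary objective section aim at insight into the situation in Switzerland.

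The recruitment detail, also under Sample characteristics, is narrower: "Eight thousand residents from the state of Basel-Stadt are to be randomly drawn", using the cantonal register, and approached by post. For the remainder, "a sample of 2,000 individuals of the general population from the Italian- and French-speaking parts of Switzerland will be recruited by a polling institute". No other source of public participants is given.

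Mode follows recruitment route. Under Survey administration, those "contacted by postal mail will receive a QR code that will take them to the online survey". Under Data collection methods, "The telephone survey in the Italian- and French-speaking parts of Switzerland will be conducted by a polling institute". Physicians are approached by email and receive a link to the online survey.

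On size, n = 2,373 for the public group "yields significant results at a 95% confidence interval and a margin of error of 2" per cent. A 30% response from 10,000 is then said to give 3,000 records, in line with a representative sample size.

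Statistical analysis lists, as the fifth secondary endpoint, a comparison of all endpoints between the public and physicians. It names group and gender as variables to control for.

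**The concern.** The description and the sampling frame do not match. Residents of German-speaking areas outside Basel-Stadt have no route into the public sample, yet the target is Swiss residents and the stated precision reads as precision about them. A margin of error covers random sampling from the frame. It says nothing about people outside it.

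Mode is also allocated entirely by region. Basel-Stadt answers anonymously on screen, while the French- and Italian-speaking regions answer an interviewer. The items cover assisted dying, social distance and coercion, where a mode effect is plausible, although the article does not quantify one. No analysis can separate region from mode when each region has only one mode.

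Two outputs are at stake: the descriptive levels for the public, and the planned public-versus-physician comparison, in which canton and mode differ between the groups as well as profession.

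**Working it through.** **Inputs.** From the article: 8,000 and 2,000 invitations, 30% response, 95% confidence, 2-point margin, n = 2,373 (public) and n = 2,258 (physicians). Assumed: p = 0.5, which is not stated.

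**1. The plan's own figure.** For a single proportion, n0 = z² × 0.25 / margin² = 1.96² × 0.25 / 0.02² = 2,400.9, so 2,401. The stated 2,373 needs a finite-population correction, n = n0 / (1 + (n0 − 1)/N). With N = 200,000, n = 2,400.9 / (1 + 2,399.9/200,000) = 2,372.4, rounded up to 2,373. Solving for N gives about 197,000 to 208,000, depending on rounding. The physician figure implies N of about 37,900 in the same way.

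A population near 200,000 cannot be Switzerland on the article's own numbers. The Introduction reports 724 assisted deaths in 2014 as 1.2% of all deaths, that is 724 / 0.012 ≈ 60,300 deaths in one year. The count itself is not the problem: for an assumed population of 5 million the formula gives 2,399.8, and 3,000 expected records exceed that.

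**2. Composition.** Invitations: 8,000 / 10,000 = 80% Basel-Stadt and 20% French- and Italian-speaking regions. Records at 30%: 0.30 × 8,000 = 2,400 online and 0.30 × 2,000 = 600 by telephone. If the 2,000 were completed interviews, the telephone share would be 2,000 / 4,400 = 45%. The article applies 30% to all 10,000, so the first reading fits better.

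**3. Margins, 1.96 × √(0.25/n), for a percentage.**

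| Stratum | n | Margin (points) |
|---|---|---|
| Pooled | 3,000 | 1.79 |
| Basel-Stadt, online | 2,400 | 2.00 |
| French/Italian regions, telephone | 600 | 4.00 |
| Each of the two regions, if split evenly (assumed) | 300 | 5.66 |

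**4. Sensitivity to coverage (illustration).** Let Basel-Stadt differ from the rest of German-speaking Switzerland by d points and make up a share s of it. Keeping the 80/20 mix fixed, the pooled figure is off by 0.80 × d × (1 − s). With d = 5 and s = 2% to 10% (both assumed), this is 3.9 to 3.6 points. The error equals the 2-point margin at d = 2 / (0.80 × (1 − s)) = 2.6 to 2.8 points. The documents give neither d nor s.

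**5. The group comparison.**

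| | Public | Physicians |
|---|---|---|
| Geography | 80% Basel-Stadt, 20% French/Italian regions | Seven cantons |
| Mode | About 80% online, 20% telephone | Online |

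One small exception: Study questionnaire moves a physician found in the public sample to the physician group, so a few telephone records could arrive there.

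**The case against.** The strongest reply is that the primary endpoint is hardly touched. Each participant rates one vignette of each illness type, with the version assigned at random. The contrast by illness type is therefore within person, and neither the frame nor the mode biases it within the sample. That stands. Only its generalisation is limited, and only if the effect differs by region or mode.

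Four further readings are tempting but unsupported:

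- *That the plan will pool without weights or a stratum term.* The article is silent on weights, and its covariate list is open-ended. These details may sit in a document that is not shown. Weights could not supply unsampled cantons or separate region from mode in any case.
- *That language-region comparisons will be spoiled.* None of the research questions or endpoints plans one.
- *That the national figure is wrong by a known amount.* The differences and shares in step 4 are assumptions. The outcome is also a 5-point rating analysed by regression, so percentage points apply only to a proportion derived from it.
- *That all French and Italian speakers are interviewed by telephone.* Mode follows region and recruitment route, not language. A French speaker in Basel-Stadt answers online, and so do physicians recruited in Ticino and Vaud.

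It is also fair to say that the article discloses the composition openly, calls the study exploratory, and uses the word representative of a sample size. Exploratory status does not, however, turn a one-canton frame into a national description.

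**Conclusion.** The concern holds for description, generalisation and the group comparison, not for the internal validity of the illness-type contrast. The public sample is Basel-Stadt (80% of invitations, online) plus the French- and Italian-speaking regions (20%, telephone), with complete overlap of region and mode. Pooled public levels of acceptance, guideline agreement and stigma should not be read as Swiss levels with a 2-point margin. The supportable precision at 30% response is about 2.0 points for Basel-Stadt and 4.0 points for the telephone stratum, assuming p = 0.5 and the same response in both. A public-versus-physician difference, as planned, cannot be attributed to profession alone. The size of any resulting bias cannot be derived from the documents.

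**What to change.** - Record recruitment stratum and mode for every record, and canton for physicians. The demographic items listed in the article name none of these and the survey is anonymous, so confirm this before data collection.
- Report Basel-Stadt (online) and the Italian- and French-speaking regions (telephone) separately as the main descriptive results, each with its own margin.
- Include the combined region/mode stratum in the models, with its interaction with illness type. The main effect alone would leave the within-person contrast essentially unchanged; the interaction shows whether the contrast carries over between strata.
- Add a sensitivity analysis of the public-versus-physician comparison restricted to online respondents in Basel-Stadt, which holds canton and mode constant.
- Drop the word representative. State that the German-language public results generalise to Basel-Stadt only and that region and mode effects cannot be separated.
- Do not present a pooled figure weighted to language-region shares as a national estimate: it would make Basel-Stadt stand for all of German-speaking Switzerland. Nor does an optional online link for telephone recruits settle the mode question, since mode would then be self-selected.

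The cost is a narrower claim, margins of 2.0 and 4.0 points in place of a pooled 1.79, and a few recorded variables. The precision of the Basel-Stadt group comparison cannot be given, because the article does not state how many of the physicians work there.

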### Eligibility criteria

The inclusion criteria for participants from the general population are (1) Swiss residents between 18 and 65 years old, and (2) sufficient knowledge of German, Italian, or French. Medical professionals are included if they are registered in one of the states (“cantons”) Basel-Stadt, Basel-Landschaft, Aargau, Lucerne, Graubünden, Ticino, or Vaud. Physicians from all specialties are to be surveyed to be able to draw a comparison between the different medical professionals.

### Data collection methods

The online survey will be created and administered using the online survey tool “Unipark” (Tivian XI GmbH, released 2020, Unipark, Köln, Germany: Tivian XI GmbH). The survey data will then be exported to Excel for storage.

The telephone survey in the Italian- and French-speaking parts of Switzerland will be conducted by a polling institute. Telephone survey data will be entered into the Unipark online survey as well and extracted to Excel for storage.

Project data will be handled with the uttermost discretion and is only accessible to authorized personnel who require the data to fulfil their duties within the scope of the research project. On the Case Report Forms (CRFs) and other project-specific documents, participants are only identified by a unique participant number. Data will be stored and used according to the Swiss Data Protection Act. The survey is anonymous, and no identifiable information will be stored. The data will be stored in an encrypted and password-protected Excel file which only the research team will have access to. They are subject to the duty of confidentiality. The data is stored in the internal clinical data system which aligns with the security standards for patient data in Switzerland.

In addition, we will regularly save a copy of this file on a CD to be able to track changes in the data at a later point in time. We keep dated and signed CDs in a safe. Only the research team can open this safe. To allow follow-up studies, the anonymized data will be kept indefinitely.

### Survey administration

Participants from the general population will be recruited via postal mail as well as via a polling institute. Medical professionals will be recruited and contacted via email.

Those participants from the general population who will be contacted by postal mail will receive a QR code that will take them to the online survey. Participants from the medical profession will be directed to the online survey via a link that they will receive by email. The QR code or link will be used to access the survey start page, where the study will be described in detail and individuals are informed regarding participation. To start study participation, individuals must click the consent button. Only then will the survey begin. Individuals who do not wish to participate may, but are not required to, provide a reason. Persons from the general population contacted by telephone will be verbally informed about the study and asked for their consent before the survey begins.

Participants can complete the online questionnaire within 3 months. Once the survey period will be completed, the data will be analyzed within approximately 3 months, discussed, and summarized in a publication within another 3 months. In total, the research project is planned to take 14 months.

### Statistical analysis

The primary endpoint will be the degree of consent to PAD depending on the type of illness (somatic vs. mental).

In addition, the following secondary endpoints have been defined:

1. Degree of consent to PAD as a function ofa. the intolerable sufferingb. DMCc. the availability of therapeutic optionsd. the terminal nature of the illness.2. Positioning of the respondents to the SAMS criteria of 2004, 2018, and 2021.a. Spontaneously expressed opinions in an open answer format in the context of a qualitative evaluation.b. Agreement or disagreement when presented SAMS criteria of 2004, 2018, and 2021.3. Association between the positioning of the respondents on the SAMS criteria of 2004, 2018, and 2021, and the evaluation of the case vignettes.4. Association between the degree of stigmatization and the assessment of PAD.5. Comparison of the primary and secondary endpoints between the two groups.

The statistical analysis of the collected data will be done with a standard statistical package, either IBM SPSS Statistics (IBM Corp, released 2020, IBM SPSS Statistics for Windows, Version 27.0, Armonk, NY: IBM Corp.) or R Studio (RStudio Team, released 2020, RStudio: Integrated Development for R. Boston, MA: RStudio, PBC). The descriptive statistics of the sample characteristics will be performed separately for the two groups and the whole sample. For binary and categorical variables, we will report frequencies in numbers and percentages; for continuous variables, we will report the mean and standard deviation, and the median and interquartile range, respectively. Given the fact that our research project is an exploratory study, we do not explicitly specify significance levels. The primary endpoint [level of PAD consent as a function of the type of illness (somatic vs. mental)] will be evaluated in a simple regression analysis with the level of PAD consent as the dependent variable and type of illness as the independent variable. In a multiple regression analysis, we will further examine the association of demographic factors such as gender with the dependent variable. The variables general population/medical professional and gender will be controlled for statistically whenever necessary. The secondary endpoints will be evaluated—as far as possible—with the same analyses. To explore the responses from the free-text fields, computer-assisted content analysis will be used (MAXQDA12; VERBI Software GmbH, Berlin, Germany).

We will test for differences between the two groups using two-tailed *t*-tests (in the presence of a normal distribution) or the Mann-Whitney U test (in the absence of a normal distribution) for continuous variables and the Chi^2^-test for categorical variables.

The model assumption will be checked in advance and the distributions of the endpoints will be plotted with scatter plots. If any model assumptions are not met, confidence intervals will be created using bootstrap. This resampling-based, non-parametric procedure can also be used if the model's normal distribution assumptions are not met.

If a participant completes the online survey entirely, missing values are not to be expected, as the survey will be designed in a manner such that it can only be completed if all fields are filled in. Missing values in incomplete surveys can be considered “data missing at random” and estimated via multiple imputations. Outliers will be identified and checked for their plausibility. If a participant drops out of the online survey this will be registered and the dropout rates of both groups will be explored. By choosing an appropriately large sample size response dropouts have been accounted for.

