### Primary objective

The current study investigates the acceptance of PAD in the general population on the one hand, and in the medical profession, on the other hand, depending on (1) the type of illness (somatic/mental), (2) the presence of intolerable suffering, (3) DMC, (4) the availability of therapeutic options, and (5) the terminal nature of the illness based on case vignettes. Furthermore, it examines to what extent the stigmatization of mentally ill persons is linked to the acceptance of their wish to die. It is an exploratory analysis to provide first insights into the current situation in Switzerland, paving the way for further research projects to form hypotheses. Within the scope of this project, the following research questions will be investigated:

Are there associations between the type of illness (somatic vs. mental) and the decision on whether a person should be granted access to PAD?Does the reasoning behind accepting the legitimacy of wishes to die correspond to the conflict between professional societies (terminal illness vs. intolerable suffering)?To what extent does the acceptance of PAD in concrete situations described in case vignettes correspond to the positioning on the SAMS criteria of 2004, 2018, and 2021?Which criteria do participants from the public and the medical profession indicate as relevant to them in an open answer format?Is there an association between the level of stigmatization and the assessment of whether a person should be granted access to PAD?Are there differences between medical professionals and the public regarding research questions 1–5?

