## Methods

### Study design

This is a monocentric prospective observational survey-based study. The study is exploratory and will consist of an online/telephone survey about PAD in somatic vs. mental illness in Switzerland on a sample of the general population from all three language regions (German, Italian, and French) as well as medical professionals working in the seven states (“cantons”) of Basel-Stadt, Basel-Landschaft, Aargau, Lucerne, Graubünden, Ticino, and Vaud. Each participant will be randomly assigned a somatic terminal, a somatic non-terminal, and a mental non-terminal case vignette. Furthermore, the attitude toward the ethical guidelines of the Swiss Medical Association of 2004, 2018, and 2022, as well as the stigmatization of mentally ill people will be assessed. The study questionnaire is described in detail below.

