#### Case vignettes and assessment of PAD

It is essential that the persons taking part in the study fully understand what is meant by PAD and this cannot be taken for granted when addressing the general population. Physician-assisted dying is therefore explained in lay terms before the questions concerning PAD are posed.

For the vignettes, three cases were created: one about a person suffering from a non-terminal somatic illness, one about a person suffering from a terminal somatic illness, and one about a person suffering from a non-terminal mental illness. For each of these cases, there will be 16 different versions. Common to all of them will be the three factors of well-consideration, self-determination, and permanence of the desire to die. In contrast, the factors tolerability vs. intolerability of suffering, DMC vs. incapacity, the absence vs. presence of a therapeutic option, and the gender of the person depicted differ and are permuted with each other in the vignettes. This will result in a total of 48 different case vignettes. Expert ratings will be used to assess the interrater reliability of the case vignettes. To ensure that the assessment of different raters has a concurrent outcome, interrater reliability is calculated using Fleiss' kappa with a target value of at least 0.8, indicating substantial agreement (22). This measure has the advantage over other kappas such as Cohen's kappa that interrater reliability by more than two raters can be tested.

Each participant will be randomly assigned three case vignettes—one (out of 16 possible variations) about a person suffering from a non-terminal somatic illness, one (out of 16 possible variations) about a person suffering from a terminal somatic illness, and one (out of 16 possible variations) about a person suffering from a non-terminal mental illness. For these three concrete situations, the participant will be asked to assess whether physician-assisted suicide should be granted or not. The participant will define the degree of his or her approval or disapproval on a 5-point Likert scale and will be asked to justify the decision by describing his or her motives in an open answer format. Furthermore, participants will be asked to select those items from a list of alternative justifications that are decisive for their judgment.

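### The primary somatic-versus-mental contrast sets a half-terminal somatic group against a never-terminal mental group, so illness type is confounded with terminality

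*Protocol article*

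**What the plan says.** The Study design section fixes what each respondent sees: "Each participant will be randomly assigned a somatic terminal, a somatic non-terminal, and a mental non-terminal case vignette". The section on case vignettes describes the same three cases, including "one about a person suffering from a non-terminal somatic illness, one about a person suffering from a terminal somatic illness". Four features are permuted within each case: suffering, decision-making capacity, therapeutic option and depicted gender. Terminality is not permuted; it belongs to the case. No mental case is terminal.

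The Primary objective section lists illness type as factor 1 and "the terminal nature of the illness" as a separate factor 5.

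The Statistical analysis section then gives illness type two levels: "The primary endpoint will be the degree of consent to PAD depending on the type of illness (somatic vs. mental"). This endpoint "will be evaluated in a simple regression analysis with the level of PAD consent as the dependent variable and type of illness as the independent" term, and that sentence names no other regressor. Two further sentences name other variables. The first reads: "In a multiple regression analysis, we will further examine the association of demographic factors such as gender with the dependent variable". The second reads: "The variables general population/medical professional and gender will be controlled for statistically whenever necessary". Neither mentions terminality, which appears only as secondary endpoint 1d. Secondary endpoints are to be analysed in the same way where feasible.

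**The concern.** With two levels and one regressor, both somatic vignettes fall on the somatic side. That side is then half terminal, and the mental side is never terminal. Randomising the 16 versions balances the four permuted features across the three cases in expectation, but it cannot balance terminality.

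The primary coefficient thus mixes two explanations: respondents may judge mental illness differently, or they may judge terminal illness differently. The Introduction explains that a terminality requirement works against mentally ill people because their illness is not usually classed as terminal. A result that cannot tell these explanations apart does not answer the question about illness type, and it could be read as evidence of unequal treatment of mental illness that the data do not contain.

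**Working it through.** **Design figures.** Four two-level features give 2^4 = 16 versions, and 3 cases x 16 = 48 vignettes, which matches the protocol. A 30% response among 10,000 people gives 3,000 respondents per group, as the Sample characteristics section states. Per group:

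| Side of the contrast | Ratings | Terminal |
|---|---|---|
| Somatic | 6,000 | 3,000 (50%) |
| Mental | 3,000 | 0 (0%) |

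**Notation.** Mean consent is SN for somatic non-terminal, ST for somatic terminal and M for mental. The terminality effect is T = ST - SN.

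**What the planned model estimates.** With equal cell sizes, least squares on a somatic/mental indicator gives

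M - (SN + ST)/2 = (M - SN) - T/2.

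It equals the like-for-like difference only if T = 0.

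**What a model that separates the factors estimates.** Adding a terminality indicator, or comparing M with SN only, gives M - SN. The two indicators correlate at -0.5 (variance inflation 1/(1 - 0.25) = 1.33), so both main effects can be estimated.

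**Size.** The protocol gives no T, so these values are assumptions, in Likert points:

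| T | True M - SN | Planned coefficient | Separated coefficient |
|---|---|---|---|
| 0 | 0 | 0 | 0 |
| 0.25 | 0 | -0.125 | 0 |
| 0.5 | 0 | -0.25 | 0 |
| 1.0 | 0 | -0.50 | 0 |
| 0.5 | -0.5 | -0.75 | -0.5 |

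On a scale rounded and clipped to 1-5, the coefficients for T = 0.5 and 1.0 shrink to about -0.20 and -0.40. The exact values depend on the baseline mean: for baselines of 2 to 4 they run from about -0.17 to -0.21 and from -0.31 to -0.41.

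**Precision.** Assume SD 1.5 and within-person correlation 0.4, with 3,000 respondents:

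- Planned contrast, mental against the mean of both somatic ratings: sqrt(1.5 x 1.5^2 x 0.6 / 3000) = 0.026.
- Mental against somatic non-terminal: sqrt(2 x 1.5^2 x 0.6 / 3000) = 0.030.
- Ratio: sqrt(2/1.5) = 1.155.

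Even T = 0.25 puts the planned coefficient 0.125/0.026 = 4.8 standard errors from zero when M = SN. With SD 1.3 and correlation 0.3, the two standard errors are 0.024 and 0.028. With SD 1.3 and correlations from 0 to 0.5, an illustrative two-sided 5% test would reject with probability 0.99 or higher at T = 0.25.

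**Endpoint 1d.** A terminal/non-terminal regression over all three vignettes gives

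ST - (SN + M)/2 = T - (M - SN)/2.

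With T = 0.5 and M - SN = -0.5 it returns 0.75 instead of 0.5.

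**Group comparison.** If physicians and the public differ in T, they will appear to differ on illness type by half of that difference.

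**The case against.** - **Pooling is inferred.** No sentence says that the somatic vignettes are merged, and an article may leave coding to a fuller document. However, the article does specify the primary model: two levels, one regressor, and no restriction on the somatic side. A later plan with another contrast would contradict it.
- **The design already holds the remedy.** This is true. Every respondent rates a non-terminal somatic case, so the fault lies in the specified analysis and not in the data to be collected.
- **The total somatic-versus-mental difference could itself be of interest**, since most mental disorders are not terminal. As description, yes. But its value depends on the 50/50 mix of somatic vignettes, which the design imposes, so it should not be read as an illness-type effect.
- **The study is exploratory and sets no significance level.** That removes the question of error rates. It does not remove bias from the estimate, and the bias does not shrink with sample size.
- **The terminal-illness versus intolerable-suffering dispute is research question 2, while the primary endpoint serves question 1.** This is fair as to labels, and suffering is permuted within every case, so its endpoint is not confounded in this way. Terminality still enters both questions.
- **The statement on endpoint 1d is conditional.** The article hedges how far the same analyses will be used. The shift arises if 1d is run over all vignettes, which nothing in the article rules out.

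**Conclusion.** The concern holds. As written, the primary coefficient is the mental versus non-terminal somatic difference minus half of the terminality effect. That identity follows from the three equally frequent cases and needs no assumption about effect sizes.

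The numerical size does rest on assumptions. For T between 0.5 and 1.0 the shift is -0.25 to -0.50 before clipping, against a standard error of about 0.03. The direction against mental illness requires that terminality raises acceptance. Only T = 0 gives no bias. Since this is the primary endpoint and the repair is a matter of wording, it should be corrected before analysis.

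**What to change.** 1. Code case type with three levels: somatic terminal, somatic non-terminal, mental non-terminal.
2. Define the primary contrast as mental non-terminal minus somatic non-terminal. A model with separate illness-type and terminality indicators gives the same contrast.
3. Define endpoint 1d as somatic terminal minus somatic non-terminal.
4. Use these two contrasts in the comparison of physicians with the general population.
5. Drop the pooled somatic-versus-mental coefficient, or report it as descriptive only.
6. State that terminality can be estimated only within somatic illness. Without a terminal mental vignette, an interaction of illness type with terminality cannot be estimated.

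The cost is a change to the wording of the endpoint and model, with no new vignettes or data. The primary contrast uses two of the three ratings, so its standard error rises by about 15% (0.026 to 0.030 under SD 1.5, correlation 0.4 and 3,000 respondents).
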